#### Duration of mechanical ventilation

The duration of mechanical ventilation outcome is evaluated according to whether the patient did or did not require ventilator assistance for a continuous number of days until fully taken off the ventilator.

#### Duration of intensive care unit (ICU) stay

The duration of ICU stay outcome is evaluated according to whether the patient did or did not stay a continuous number of days in the ICU before being definitively discharged from the ICU.

#### Duration of hospital stay

The duration of hospital stay outcome is evaluated according to whether or not the patient stay in hospital for a continuous number of days before being definitively discharged from hospital.

#### Occurrence of other infection-related complications

Occurrence of other infection-related complications may be present when the patient is diagnosed as having infection of the urinary tract, phlebitis, cellulitis, a pulmonary abscess, tracheostomy wound infection, sepsis, septic shock, or fungemia.

#### Other respiratory complications

The respiratory complications considered are atelectasis, pneumothorax, broncospasms, bronco-aspiration, pneumomediastinum, subcutaneous emphysema, hemothorax, decompensation of chronic obstructive pulmonary disease, acute pulmonary embolism, and empyema.

#### Adverse effects of methylprednisolone

Possible adverse effects of methylprednisolone include gastro-intestinal bleeding with a drop in hematometry, fungal infection, Herpes zoster, bacterial infection, hyperglycemia, and systemic arterial hypertension (TA > 149 × 90 mmHg).

### Population

Patients who fulfill the diagnostic criteria for leptospirotic pneumonitis are included. Patients are excluded if they are aged less than 15 years, have a history of hypersensitivity to corticosteroids, have an active infection of fungal, tuberculosis or bacterial origin other than the leptospira infection, have hemoconcentration or lymphocytic atypia on admission to hospital, have co-morbidities that may be responsible for changes in radiological and gasometric examinations used to diagnose leptospirotic pneumonitis, present evidence of recent cranial trauma, neurosurgery or a peptic ulcer, or if they are taking part in another clinical trial.

### Participant recruitment

The study will cover patients admitted to the intensive care unit, or to the infectious diseases or internal medicine ward in the Oswaldo Cruz University Hospital, Barão de Lucena Hospital and Clinics University Hospital. During the study, the recruitment of patients from other hospitals will be allowed.

### Ethical considerations

The study was approved by the Research Ethics Committee, according to the resolutions of the National Health Council (FR - 167386) and was monitored by an external data monitoring committee throughout.

### Sample size

The sample size was calculated on the basis of a statistical significance (alpha error) of 5%, a power of 80%, corresponding to a beta error of 20%. The expected mortality for leptospirotic pneumonitis is 30%. For a reduction of 50% in mortality, the expected mortality in patients treated with corticosteroids would be 15%. The sample size calculated was 133 patients for each group. The same parameters were used to obtain statistical significance and a standard deviation of 21 days for duration of mechanical ventilation, giving an expected sample of 33 patients per group. For the duration of ICU stay variable, the same parameters were used to obtain statistical significance and a standard deviation of 8 days, giving an expected sample of 23 patients per group.

### Randomization

The patients with clinical symptoms of leptospirosis admitted to ICUs and hospital wards covered by the study are evaluated by doctors involved in the study to establish the extent to which they meet the criteria for diagnosis of leptospirosis and leptospirotic pneumonitis. Once this has been established, the patient is informed of the study and inclusion depends on his or her consent (signed informed consent), or, if this is not possible, on that of their relatives or legal guardians. The randomization was carried out in advance by drawing lots. The groups to which the patients are allocated are placed in sealed numbered envelopes that are only opened after the informed consents have been signed. The envelopes are opened by a third party not involved in assistance of the patients. Block randomization within each severity stratum is performed in each hospital unit. The degree of severity is stratified according to the APACHE II score. Blocks of ten are used.

### Operationalization of the Study

The study involves three hospitals and their respective intensive care units and wards for internal medicine and infectious diseases. A coordinating physician is assigned to each hospital to organize evaluation, inclusion and follow-up of the patients for the duration of the study. Two supervising doctors oversee the development of the study by way of monthly meetings with the coordinators of each hospital. To ensure that the study is double-blind, the preparation of the methylprednisolone and of the placebo is carried out in each hospital's pharmacy, duly coded and known only to the nurse involved in the study. The patients in the control group receive an infusion of saline solution identical in volume to that of the dilution received by the intervention group. The nurse involved in the study fill in a card identifying which patients received the placebo and which the methylprednisolone. This card is stored by a physician who did not treat the patients nor takes part in the investigation and will only be opened at the end of the study.

### Standardization of Treatments

All the patients included receive the conventional treatment for leptospirosis, which is the basic care provided for severely ill patients, such as volemic reposition, antibiotics, control of hemodynamics, correction of electrolytic and acid-base disorders, transfusion of hemoderivatives, hemodialysis, early and adequate nutrition, oxygen treatment, and artificial ventilation, when necessary, along with others that are commonly recommended. Decisions regarding the use of drugs and invasive or non-invasive procedures are taken by the patients' attending physicians, in accordance with current good medical practice, based on data from the literature. In view of the high doses of corticosteroid used, all patients are given an anti-parasitic drug (albendazol) and gastric protection (H2 blocker). The specific items of the treatment of leptspirosis are standardized as follows:

• Volemic reposition and the use of vasoactive drugs for lungs congested by pneumonitis follow the criteria established in the algorithms given in Appendices II and III.

• Treatment with antibiotics involves the administration of crystalline penicillin at a dose of 1,500,000 international units every six hours for all patients, regardless how long they have had the disease, or with a 1 g dose of ceftriaxone every twenty-four hours in those allergic to penicillin or where the use of penicillin is not possible. Antimicrobial treatment for associated infections is carried out according to specific recommendations^13,14,31^.

• The recommendation for platelet transfusion is calculated on the basis of one unit of platelet concentrate per 10 kg of the patient's weight, every twelve or eight hours, according to the following criteria: a platelet count (PC) less than or equal to 20,000/mm^3 ^even in the absence of bleeding; a PC of less than or equal to 50,000/mm^3 ^in cases of more severe bleeding and/or when invasive surgery or biopsies are required^15 ^and PC <100,000/mm^3 ^in cases where major surgery has been performed.

• Hemodialysis is carried out according to the recommendations outlined in the algorithms contained in Appendices II and III.

• Mechanical ventilation, where necessary, is used in controlled volume mode (VCV with a flow rate of 6 ml/kg, to generate a maximum plateau pressure of 30 cmH_2_O and a maximum inspiratory peak of 45 cmH_2_O) or controlled pressure (PCV with maximum pressure of 30 cmH_2_O), and with final positive expiratory pressure sufficient to maintain the lowest possible fraction of inspired oxygen (FiO_2_) (the ideal PEEP calculated according to the routine of the hospital ubit: PEEP curve X static complacency; pressure curve X volume; or a test of different PEEPs under SpO_2 _monitoring)^2,3,18,42^.

### Statistical analysis

Double data enter is performed using EPI INFO Version 6.0, giving rise to two datasets that can be compared to detect possible typing errors. The dataset is subsequently checked for consistency. The distribution of potential confounding factors in the two treatment groups are compared to check randomization.

The main analysis will be carried out through comparison of the various outcomes in the two groups, by calculating the percentage distribution and the relative risk. The 95-% confidence interval and the chi-squared test will be used to test statistical association. The t-test will be used to compare the means. The results are considered statistically significant when the p-value is less than 0.05. The efficacy of the intervention is calculated according to the following formula:

Patients randomly included in the study who, for whatever reason, including transfer to another hospital, do not receive the treatment for which they were assigned are considered to belong to the group to which they were allocated **(intention to treat analysis)**. These will be deemed treatment failure. The patients who do not receive confirmation from the laboratory of diagnosis of leptospirosis will still be included in the analysis. They will not be considered as losses or treatment failure. Data analysis will be carried out using EPI INFO Version 6.0 and SPSS 8.0.

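### Randomisation is stratified by APACHE II severity within hospital, but the stated mortality test is unstratified; if severity predicts death, the test is conservative and some power is given up

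*Protocol article*

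**What the plan says.** **Design.** The Randomization section of the protocol article states: "Block randomization within each severity stratum is performed in each hospital unit". It adds: "The degree of severity is stratified according to the APACHE II score". The block size is ten. The cut-points and the number of severity strata are not given.

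**Analysis.** The Statistical analysis section bases the main analysis on percentages and the relative risk in the two groups, and continues: "The 95-% confidence interval and the chi-squared test will be used to test statistical association". Means are compared by t-test. The decision rule is: "The results are considered statistically significant when the p-value is less than 0.05". APACHE II stratum and hospital are not mentioned. Prognostic factors appear only in a comparison of the arms meant as a check on the randomisation, and that comparison feeds no estimate or test.

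**Sample size.** The Sample size section plans 133 patients per group for 30% against 15% mortality, with 5% alpha and 80% power. This is also an unstratified calculation.

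**The concern.** Blocking within strata keeps the arms nearly equal in severity mix, so differences in risk between strata add almost nothing to the sampling variance of the treatment difference. The variance in an unstratified chi-squared test, or in an unstratified interval for the relative risk, still contains that between-stratum component. When the strata predict death, the standard error used is therefore larger than the real one. The test rejects less often than 5% under the null, and the interval covers more than 95%.

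What is at stake is precision on the primary outcome. The planned effect is a halving of mortality. A smaller true benefit is easier to miss with a test running at about 3% than with one running at 5%.

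**Working it through.** **1. The plan's own figure.** Inputs from the Sample size section: 30% v 15%, two-sided 5% (sidedness is not stated; only a two-sided calculation gives 133), 80% power. The mean risk is 0.225.

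- Uncorrected: n = [1.960·√(2·0.225·0.775) + 0.8416·√(0.30·0.70 + 0.15·0.85)]² / 0.15² = 120.5.
- Continuity-corrected: (120.5/4)·[1 + √(1 + 4/(120.5·0.15))]² = 133.5, against 133 stated.

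The planned size is reproduced. Without the correction, 133 per group gives 83.8% power.

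**2. Assumptions.** Mortality by APACHE II stratum is not in the documents. I take equal-sized strata with a mean control risk of 30%, and a relative risk of 0.5 in every stratum for the power figures.

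**3. Closed form under the null, with arms exactly balanced within strata.** The unstratified test uses variance p(1−p) = 0.30·0.70 = 0.21. The variance actually operating is the mean of pₛ(1−pₛ) over strata. With R = within-stratum variance / 0.21, the real type I error is 2·[1 − Φ(1.960/√R)].

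Example, 10/50%: within = (0.09 + 0.25)/2 = 0.17; R = 0.810; 1.960/0.900 = 2.178; type I error = 2.9%.

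**4. Closed form for power at 133 per arm, 10/50% falling to 5/25%.**

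- True SD of the difference: √[(0.17 + 0.1175)/133] = 0.0465.
- Unstratified null SE: √(2·0.225·0.775/133) = 0.0512. Power = Φ[(0.15 − 1.960·0.0512)/0.0465] = 86%.
- Stratified null SE, from stratum mean risks 0.075 and 0.375: √[2·0.1519/133] = 0.0478. Power = Φ[(0.15 − 1.960·0.0478)/0.0465] = 89%.

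**5. Simulation of the actual scheme.** N = 266, blocks of ten, severity strata by three hospitals (assumed shares 50/30/20%, no hospital effect on mortality). Each pair is the uncorrected chi-squared test v Cochran-Mantel-Haenszel (CMH).

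| Control risks by stratum | R | Type I, closed form (chi-squared) | Type I, simulated | Power, simulated |
|---|---|---|---|---|
| 30/30% (not prognostic) | 1.000 | 5.0% | 5.1% v 5.1% | 84.3% v 84.1% |
| 20/40% | 0.952 | 4.5% | 4.6% v 5.1% | 84.7% v 85.2% |
| 15/45% | 0.893 | 3.8% | 3.9% v 4.9% | 85.0% v 86.6% |
| 10/50% | 0.810 | 2.9% | 3.1% v 5.1% | 86.2% v 89.1% |
| 5/25/60% | 0.754 | 2.4% | 2.7% v 5.2% | 86.4% v 90.1% |

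Repeat runs moved these figures by about 0.3 points at most. Simulated type I error lies slightly above the closed form because unfinished blocks leave some imbalance within strata. With the Yates correction the unstratified test has about 80 to 83% power, but part of that gap from CMH comes from the correction itself.

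**6. Interval width.** In a smaller simulation (8,000 trials per scenario), the mean SE of the log relative risk under the null at 10/50% was 0.189 unstratified and 0.170 stratified. Coverage was 97.5% against about 95.6%. At 20/40% the unstratified coverage was 96.0%.

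**The case against.** **This is not an error of validity.** A reader might infer that the p-values are unsound or that the trial is underpowered. Neither follows. Type I error is at or below 5% apart from simulation noise, the planned size is reproduced, and the stated test keeps at least the planned 80% power in every scenario, with or without Yates. This stands in full.

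**The size rests on inputs the documents lack.** A reader might infer that the test certainly runs well below 5%. It does so only if the strata separate risk strongly. At 25/35% the two tests could not be told apart in simulation (5.1% type I error and 84.6% power for both), and at 20/40% the gain is half a point. This also stands, so the claim has to be conditional.

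**A constant relative risk favours CMH.** If the same overall benefit falls only on the severe stratum (15/45% becoming 15/15%), power is 84.9% v 85.4%, a gain of 0.5 points. The gain shrinks but does not reverse.

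**The detail may sit in an unseen analysis plan.** The article never calls its test unadjusted, and it is a condensed account. This softens the point without removing it: the article names the main analysis, effect measure, test and significance rule, and those named do not use the named strata.

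**Pooling hospitals whenever cells turn out sparse would let the primary analysis be chosen after the data are seen.** This is right, and more so because the Participant recruitment section allows further hospitals to join. The rule has to be fixed beforehand.

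**Secondary outcomes.** The calculations cover mortality only. Nothing here measures a loss for the t-test outcomes.

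**Conclusion.** The point holds as a conditional loss of efficiency. The stated main analysis does not use the strata by which patients are randomised. If APACHE II stratum predicts death, the unstratified test is conservative: about 4.6% down to 2.7% type I error over assumed control risks from 20/40% to 5/25/60%, with about 0.5 to 4 points of power given up. With non-prognostic strata the loss is nil.

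The direction follows from the design. The size rests on assumed stratum risks, equal-sized strata, a common relative risk and no hospital effect; if hospitals differ in mortality, the loss would be somewhat larger. The change is worth making because it is free, not because the trial's conclusion is in danger without it.

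**What to change.** Before unblinding, amend the Statistical analysis section so that:

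- the primary mortality analysis is the Cochran-Mantel-Haenszel test with a Mantel-Haenszel relative risk and 95% confidence interval, stratified by the APACHE II strata used at randomisation and by hospital;
- those APACHE II strata are named in the analysis text, since the article does not define them;
- any rule for pooling small hospitals is written down in advance and makes no reference to outcomes by arm (for example, a threshold on the number randomised per hospital);
- the unstratified chi-squared test and relative risk are reported as supportive.

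The relative risk remains the effect measure. The cost is wording only: no more patients and no new data, because stratum and hospital must be known to randomise each patient. The sample size needs no change on this account.

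### T-tests on ventilation, ICU and hospital days give a comparison distorted by unequal death when mortality is planned at 30% v 15%, in a direction and size that the documents do not settle

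*Protocol article*

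**What the plan says.** The three outcomes are defined under their own headings in the Protocol article. Ventilation is counted "for a continuous number of days until fully taken off the ventilator". ICU stay is assessed by whether the patient did or did not "stay a continuous number of days in the ICU before being definitively discharged from the ICU". Hospital stay is counted "for a continuous number of days before being definitively discharged from hospital". A patient who dies before weaning or discharge does not reach these end events. The Study design section ends follow-up at discharge or death.

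The Sample size section plans mortality of 30% on control and 15% on methylprednisolone, and concludes: "The sample size calculated was 133 patients for each group". It also sizes ventilation from an SD of 21 days (33 per group) and ICU stay from an SD of 8 days (23 per group), so both are intended as comparisons of means.

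The Statistical analysis section offers relative risks, confidence intervals and the chi-squared test for proportions, and for the rest: "The t-test will be used to compare the means". It deems patients who do not receive their assigned treatment to be treatment failures, but this gives no value in days. No time-to-event, competing-risk or free-days analysis is named.

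**The concern.** The plan expects half as many deaths on treatment as on control, then compares days to an event that death prevents. Either way of handling deaths causes trouble:

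- **Counted up to death.** An early death enters as a short stay. The arm with more deaths looks better on duration whenever those who die have shorter stays than survivors.
- **Dropped.** The t-test compares survivors. If treatment halves mortality, its survivors include patients who would have died on control, so the two groups are no longer comparable by randomisation.

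A beneficial treatment could therefore appear to prolong ventilation or stay, and a harmful one could appear to shorten them. Three of the eight secondary outcomes are exposed to this, just when the primary outcome shows an effect.

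**Working it through.** **The plan's own figure.** For 30% v 15%, two-sided 5% (sidedness is not stated) and 80% power, the two-proportion formula gives 121 per group without continuity correction and 134 with it. The stated 133 is reproduced within rounding. The sample sizes for the durations cannot be checked forwards because no difference to detect is stated. Solving backwards gives about 14.5 days (SD 21, 33 per group) and 6.6 days (SD 8, 23 per group).

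**Deaths counted up to death.** Let S be the mean stay of survivors and D that of patients who die, both unaffected by treatment.

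- Control mean = 0.70 S + 0.30 D
- Treated mean = 0.85 S + 0.15 D
- Difference (treated - control) = 0.15 x (S - D)

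S and D are not in the documents. Assumed values, all with no true effect on duration:

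| S | D | Control | Treated | Difference (days) |
|---|---|---|---|---|
| 10 | 5 | 8.50 | 9.25 | +0.75 |
| 14 | 6 | 11.60 | 12.80 | +1.20 |
| 14 | 4 | 11.00 | 12.50 | +1.50 |
| 20 | 5 | 15.50 | 17.75 | +2.25 |
| 10 | 10 | 10.00 | 10.00 | 0 |
| 10 | 15 | 11.50 | 10.75 | -0.75 |

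A real gain is also hidden. With S = 14, D = 6 and survivors' stay cut by 2 days on treatment, the treated mean is 0.85 x 12 + 0.15 x 6 = 11.1. Against 11.6 the difference is -0.5 day, not -2.

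**How often the t-test would be significant against treatment** (S = 14, D = 6, difference 1.2 days). By normal approximation the chance is 1 - Φ(1.96 - 1.2/SE), with SE = SD x √(2/133):

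- SD 11: SE 1.35, chance 14%
- SD 21 (the plan's ventilation SD): SE 2.58, chance 7%

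Simulated t-tests on lognormal durations agree:

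- 133 ventilated per arm, coefficient of variation 0.9 (control SD about 11): about 13% to 15%
- same, with the spread raised to an SD of about 19 to 21: about 6% to 7%
- coefficient of variation 0.9, fewer ventilated: about 9% at 66 per arm, 7% to 8% at 50, and 6% to 7% at 40
- 133 per arm, coefficient of variation 0.9, D raised to 10 days: 5% to 6%; D = 14: 2.5% each way; D = 18: the bias reverses to about -0.6 day

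If mortality instead rose from 15% to 30% on treatment, the base case gives about -1.2 days and a significant apparent benefit in about 14% of trials.

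For ICU stay the plan's SD is 8 days. If the same S and D held there, SE = 0.98 and the chance is 23%. A smaller SD makes the same shift easier to detect.

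**Deaths dropped.** Suppose treatment saves 15 in every 100 patients and causes no deaths. The saved patients are then 0.15/0.85 = 17.6% of treated survivors and have no counterpart among control survivors. If their mean stay is M, the survivor means differ by 0.176 x (M - S) with no effect on anyone else's stay. M is unknown.

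**Free days.** In the same base-case simulations, ventilator-free days to day 28 moved by about +2.3 (mortality lowered), -2.3 (mortality raised) and +3.6 (mortality lowered and survivors 2 days shorter), the right direction each time.

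**The case against.** - **Omission.** How deaths enter a duration is often left to the analysis plan, and this is a condensed article. The t-test sentence does not name the durations. It is true that a missing rule alone would be no finding. But the article fixes both the definitions and the test, the SD-based sizing ties two of the durations to means, and neither obvious rule for deaths repairs a t-test on raw days.
- **Size.** Assuming that all 133 per arm are ventilated is generous: recruitment includes wards, and ventilation is given only where needed. An SD of 11 is also well below the plan's 21. This stands, which is why a range is given. If never-ventilated patients entered as zero, the rate with 30% to 50% ventilated would be about 5% to 6%.
- **Direction.** A reader might infer that a life-saving steroid must look harmful on these outcomes. The documents do not support that, because they give no stay by vital status.
- **Skew.** A reader might also infer from the SD of 21 days that ventilation times are strongly skewed. No mean is given, so this does not follow and forms no part of the point.
- **Meaning.** Length of stay has a legitimate resource-use reading, in which more survivors staying longer is a true result. That is fair, but these durations are listed as outcomes of an efficacy trial.
- **Remedy.** Free days turn a mortality effect into an apparent ventilation gain: +2.3 days with no change in survivors' weaning. This stands and is met by reporting the components.

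**Conclusion.** The point holds as a structural fault in how three secondary outcomes are to be analysed. With mortality of 30% v 15%, a comparison of mean days is distorted by 0.15 x (S - D) if deaths are counted up to death, and is confined to a post-randomisation subgroup if they are dropped.

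The size rests on assumptions. With S = 14 and D = 6, the treated mean for ventilation is about 1.2 days longer with no true effect on survivors' duration, and significant apparent harm arises in about 6% to 15% of trials against 2.5% nominal. There is no distortion if S = D, and it reverses if those who die stay longer. The fault itself is certain; its direction in this trial is not.

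The mortality analysis and the 133 per group are unaffected. The change should be made, but the trial's main conclusion does not depend on it.

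**What to change.** In the Statistical analysis section, replace the t-tests on these outcomes:

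- **Ventilation and ICU stay:** ventilator-free and ICU-free days to day 28 in all randomised patients, with death scored 0 and survivors never ventilated (or never in ICU) scored 28. Compare by a rank test stratified by hospital and APACHE II stratum, matching the randomisation.
- **Hospital stay:** time to discharge alive, with death as a competing event.
- **Status after discharge:** follow-up stops at discharge, so state the assumption that patients discharged before day 28 remain alive, off the ventilator and out of ICU to that day.
- **Components:** report mortality, and durations separately in survivors and in deaths, descriptively beside each result.

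The cost is a change of wording and analysis. The dates needed are those that the durations and mortality already require, but the count to day 28 depends on the assumption about discharged patients. The main drawback is that free days mix mortality with duration, so a gain cannot be read as faster weaning without the components.

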## Methods/Design

### Study design

The study is a double-blind randomized clinical trial - RCT--which evaluates the efficacy of the use of pulse therapy with methylprednisolone compared to a placebo in patients with lung involvement in leptospirosis. The patients are randomly divided into two clearly-defined groups: a) the study group, which receives conventional treatment associated with endovenous pulse therapy with 1 g methylprednisolone for three consecutive days and b) the control group, which receives the conventional treatment plus a placebo. The patients are followed until such a time as they are discharged from hospital or die. The primary endpoint is taken to be mortality from leptospirotic pneumonitis. The secondary end-points are: a) evolution of lung disease; b) the occurrence of nosocomial respiratory infection; c) duration of mechanical ventilation; d) duration of intensive care unit (ICU) stay; e); duration of hospital stay; f) occurrence of other infection-related complications; h) Other respiratory complications; and i) adverse effects of methylprednisolone.

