#### Mortality

The mortality outcome is defined as death caused leptospirosis related or not to leptospirotic pneumonitis.

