The evolution of hematometry is measured by way of hematocrit and hemoglobin levels and considered when there is a decrease of over three percentage points in hematocrit and 1 g/dl in hemoglobin, with no evidence of blood loss. The intensity of bleeding from the lungs is categorized as slight, when the hematocrit loss is more than three and less than five percentage points, moderate when greater than five but less than ten percentage points, and severe when it is greater than ten percentage points. The evolution of hematometry is evaluated on the fifth day of the patient's follow-up and is categorized as having improved when there has been no drop in hematometry or when it is kept in levels considered acceptable, when blood transfusion is necessary. It is considered to have declined when the hematometry remains unchanged after hemotransfusion or when there is an increased drop in hematometry.

Patients are considered to have improved, irrespective of the extent of the improvement, when, after five days of follow-up, there has been an improvement in three of the four parameters evaluated: lung auscultation, radiological evaluation of pulmonary infiltrate, arterial gasometry and hematometry. Improvement is considered to be early when it occurs within the first forty-eight hours and late when it occurs later than this. Treatment is considered to have failed when the patient does not show improvement in three of the four parameters listed above.

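### Patients who do not receive their assigned treatment are scored as failures whatever happened to them, for no named endpoint, under an intention-to-treat label

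*Protocol article*

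**What the plan says.** All places are in the protocol article.

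- **Statistical analysis, who is covered.** The rule applies to any randomised patient whose assigned course was not given, whatever the cause, and transfer is the one cause mentioned. On group membership, these patients "are considered to belong to the group to which they were allocated". The article labels this intention to treat.
- **Statistical analysis, what is done with them.** The next sentence reads "These will be deemed treatment failure". It has no condition on whether the outcome is known, and it names no endpoint.
- **Statistical analysis, a contrasting rule.** Patients without laboratory confirmation of leptospirosis stay in the analysis, and "They will not be considered as losses or treatment failure". Failure is therefore an analysis status separate from group membership.
- **Evolution of lung disease.** This is the only place where failure is defined, and it concerns a secondary endpoint: "Treatment is considered to have failed when the patient does not show improvement in three of the four parameters listed above".
- **Mortality (primary outcome).** "The mortality outcome is defined as death caused leptospirosis related or not to leptospirotic pneumonitis".
- **Study design.** "The patients are followed until such a time as they are discharged from hospital or die".

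**The concern.** The first half of the rule is intention to treat. The second half is not, because it replaces the patient's outcome with one derived from adherence. The trigger is non-receipt, not a missing outcome. A patient who misses the infusions, stays in hospital and goes home alive is covered, although follow-up to discharge makes vital status known. A patient who receives every infusion and is then transferred with outcome unknown is not covered.

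Two things are at stake. If non-receipt is equal in the two arms, imposed failures add the same block of events to both, which pulls the relative risk towards 1 and costs power. If it is unequal, the difference in non-receipt enters the comparison as a difference in outcome, so an inactive drug can look harmful or beneficial. How far this reaches depends on the endpoint, which the text leaves open.

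**Working it through.** **1. Which endpoint?** Two readings are possible.

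- *Lung evolution.* Failure is defined only there, as lack of improvement in three of four parameters. The rule then overrides that assessment when it was made, and departs from the article's own definition: a non-receiver who improved on all four parameters would be scored a failure. The article gives no expected rate for this endpoint, so no size can be computed.
- *All outcomes, including death.* The rule stands in the section whose main analysis compares the various outcomes by relative risk and chi-squared test. A non-receiver known to have survived would then count with the deaths.

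All figures below are conditional on the second reading.

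**2. Inputs.** From Sample size: mortality 30% (control) and 15% (active), alpha 5%, power 80%, 133 per group. From Statistical analysis: relative risk and chi-squared test. The article gives no non-receipt rate *f*, so 2%, 5% and 10% are assumptions.

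**3. The plan's own figure.** For a two-sided test with mean rate 0.225:

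n = [1.960·√(2·0.225·0.775) + 0.842·√(0.30·0.70 + 0.15·0.85)]² / 0.15² = 120.5

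With continuity correction:

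n/4·[1 + √(1 + 4/(n·0.15))]² = 133.5

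This is 134 if rounded up, so the stated 133 reproduces. By exact enumeration of the chi-squared test at 133 per arm, power with no non-receipt is 84% (80% with Yates correction).

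**4. Equal non-receipt in both arms.**

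- Rule as written: each arm's rate becomes f + (1 − f)·p.
- Observed outcomes: control stays at 0.30; active becomes (1 − f)·0.15 + f·0.30, taking untreated patients to have control risk.

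Example at f = 10%. Rule: 0.10 + 0.90·0.30 = 37.0% v 0.10 + 0.90·0.15 = 23.5%, RR 0.635. Observed: 30.0% v 16.5%, RR 0.55.

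| f | Rates, rule | RR, rule | RR, observed | Power, rule (Yates) | Power, observed (Yates) | Risk difference, both |
|---|---|---|---|---|---|---|
| 2% | 31.4 v 16.7% | 0.53 | 0.51 | 81% (76%) | 83% (78%) | 14.7 points |
| 5% | 33.5 v 19.25% | 0.575 | 0.525 | 76% (71%) | 80% (75%) | 14.25 points |
| 10% | 37.0 v 23.5% | 0.635 | 0.55 | 68% (62%) | 75% (70%) | 13.5 points |

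The rule's own cost in power is about 2, 4 and 7 points. The rest of the fall from 84% is the ordinary effect of patients going untreated. The risk difference shrinks by the factor (1 − f) under both approaches.

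**5. Unequal non-receipt, no drug effect, 30% mortality in both arms.** Rates are f + (1 − f)·0.30.

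| Non-receipt | Rates under the rule | Type I error (Yates) |
|---|---|---|
| 2% v 4% | 31.4 v 32.8% | 5.8% (4.2%) |
| 2% v 5% | 31.4 v 33.5% | 6.6% (4.9%) |
| 5% v 10% | 33.5 v 37.0% | 9.2% (7.1%) |
| 3% v 10% | 32.1 v 37.0% | 13.4% (10.6%) |

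With observed outcomes the rate is 30% in both arms whatever the imbalance, and the error is about 5% (about 4% with Yates). The direction follows the arm with more non-receipt: at 5% v 10% the relative risk is 33.5/37.0 = 0.905 if the active arm has less, and 37.0/33.5 = 1.10 if it has more.

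**The case against.** The strongest reply is that the article never equates treatment failure with death. Mortality has its own definition, and failure is defined only for lung evolution. Read that way, the rule touches one binary secondary endpoint, where counting non-receivers as non-responders is a recognised convention, and the mortality sample size is untouched. This stands as a limit on the figures: a reader might infer that the plan counts survivors as deaths, but the document does not say so. It does not rescue the sentence, which names no endpoint and sits under the main analysis of all outcomes. Even the narrow reading overrides observed assessments under an intention-to-treat label.

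Three further points stand in part.

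- A reader might conclude that the planned 80% power is lost, or compare the diluted relative risk with 0.50. Neither is fair. Any intention-to-treat analysis dilutes when patients go untreated, so the comparator is 0.51 to 0.55. At 2% non-receipt the uncorrected power is still 81%.
- The infusions are coded and volume-matched (Operationalization of the Study), so large imbalance in non-receipt is less likely. It is not excluded, but the unequal scenarios are illustrations. At 2% v 4–5% the inflation is slight, and with Yates correction the error stays below 5%.
- Not every covered outcome is observable. Transfer is the one reason that the rule names, and day-5 auscultation, radiology and gasometry may not be available from another hospital. For those patients the rule works partly as imputation. That justifies a rule for missing outcomes, not one triggered by non-receipt.

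**Conclusion.** The point holds. The rule assigns outcomes from non-receipt, whether or not they were observed, contradicts the intention-to-treat label, and leaves its endpoint unstated. What is certain is that it overrides the lung-evolution assessment and departs from the article's own definition of failure. What is conditional is any effect on mortality. If the rule is applied there, and non-receipt is equal at 2% to 10%, it costs about 2 to 7 points of power and moves the relative risk from 0.51–0.55 to 0.53–0.635, leaving the risk difference as it would be with observed outcomes. With unequal non-receipt and no drug effect, it raises the type I error from about 5% to about 6–7% at 2% v 4–5%, 9% at 5% v 10% and 13% at 3% v 10% (11% with Yates correction), with bias possible in either direction. All non-receipt rates are assumptions. The documents do not support saying that the primary analysis will count survivors as deaths, only that the wording allows it.

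**What to change.** Delete the sentence that deems these patients failures. In its place, state that:

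1. every randomised patient is analysed in the allocated group with the outcome actually observed, for mortality and for lung evolution;
2. vital status is sought from the receiving hospital for transferred patients;
3. imposed failure is used only where the outcome is truly unobserved (for example, day-5 lung status after transfer), for a named endpoint, with best-case and worst-case sensitivity analyses.

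The cost is a short change to the analysis section, a few follow-up enquiries and a little more analysis work. The sample size need not change on this account.
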